### Data collection

At enrollment, before the sigh test we will anonymously collect patients’ demographic information (e.g., age, sex, height, weight), past (e.g., hypertension, chronic medications) and recent (e.g., etiology of the acute respiratory failure, days since intubation) medical history, severity of lung injury (e.g., ventilation setting, arterial blood gases, respiratory system compliance, diagnosis of acute respiratory distress syndrome (ARDS)) and of systemic involvement (e.g., presence of shock, number of organ failures) and finally, ventilation data (e.g., RR, Vt, PEEP, FiO_2_, PSV level).

In both groups, for the first 24 h, we will assess the SpO_2_/FiO_2_ ratio, RR and PSV tidal volume every 4 h to further characterize physiologic response to sigh over time.

From day 1 (i.e., within 24 h from randomization) to day 28 or death or discharge from the ICU, the following data will be collected every day between 6:00 and 10:00 in the morning: arterial SpO_2_, arterial and central venous blood gas analyses, ventilation settings and pattern (i.e., sigh pressure level, sigh tidal volume, PSV level, PSV tidal volume, respiratory rate, PEEP, FiO_2_, minute ventilation, P0.1, mean airway pressure), heart rate, arterial blood pressure, central venous pressure, cumulative fluid balance, patient’s comfort assessed using a visual analog scale (VAS), RASS value, SOFA score and dosage of sedative agents and vaso-active drugs.

Moreover, each day we will collect information on use of rescue treatments (i.e., recruitment manoeuvers, use of PEEP ≥ 15 cmH_2_O, prone positioning, inhaled nitric oxide, extracorporeal membrane oxygenation), tracheostomy, switch from the allocated treatment to the other study arm for ≥ 24 h, switch to controlled ventilation for ≥ 24 h, reason for switch to controlled ventilation, adverse events (i.e., hemodynamic instability with hypotension with SBP < 90 mmHg despite vasoactive drugs; arrhythmias; radiographic evidence of barotrauma with pneumothorax, pneumomediastinum, pneumatocoele, or subcutaneous emphysema), SBT performance and reason for SBT failure, extubation or separation from mechanical ventilation, reintubation and reason for reintubation with time. We will collect data on day 28 for all enrolled patients on mortality, extubation that occurred outside the ICU and readmission to ICU.

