### Sample size

The sample size was computed based on the hypothesis that PSV + sigh might decrease the rate of failure of assisted ventilation compared to standard PSV. Based on previous data [21], the expected proportion of failure in patients undergoing PSV will be 22% and we hypothesized a proportion of 15% for patients in the PSV + sigh group. Assuming non-inferiority of PSV + sigh treatment, with a tolerance of 5% we estimated that a sample size of 258 patients (with 129 patients per study arm) will be sufficient to assess feasibility of the PSV + sigh strategy in this pilot phase with power of 0.8 and alpha 0.05.

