### Statistical analysis

Continuous normally distributed variables will be expressed by their mean and standard deviation or as medians and their interquartile ranges when not normally distributed. Categorical variables will be expressed as number and proportion (%). To assess the feasibility of PSV + sigh as compared to PSV (i.e., the primary endpoint), we will compute the proportion of patients experiencing at least one of the following events in each arm: switch to controlled ventilation for ≥ 24 h consecutively; use of PEEP ≥ 15 cmH2O, prone positioning, inhaled nitric oxide, extracorporeal membrane oxygenation or reintubation within 48 h from extubation.

We will compare the two proportions using the one-tailed non-inferiority test for proportions with a 5% tolerance. We will use 0.05 as the significance level. The same method will be adopted to evaluate the safety of PSV + sigh, which is a secondary endpoint. Prevalence of sigh responders in the two arms will be compared using the chi-squared or Fisher’s exact test. Ventilator-free days will be calculated as the difference between the duration of follow up (up to 28 days) and the number of days of intubation before successful extubation or separation from mechanical ventilation for tracheostomized patients. For all the secondary endpoints, we will use the chi-squared or Fisher’s exact test in the case of binary variables or the *t* test or Wilcoxon signed rank test for continuous variables. Time to death or extubation will be analyzed using Kaplan-Meier survival curves. Adjustement for potential confounding factors will be evaluated using appropriated regression models.

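### The unadjusted primary non-inferiority test is valid and adequately sized, but it forgoes modest precision available from baseline data already recorded before randomisation

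*Protocol article*

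**What the plan says.** All references are to the protocol article.

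- **Primary test (Statistical analysis).** "We will compare the two proportions using the one-tailed non-inferiority test for proportions with a 5% tolerance", at a significance level of 0.05. No covariate enters this test.
- **Adjustment (last sentence of the same section).** "Adjustement for potential confounding factors will be evaluated using appropriated regression models". The sentence follows the secondary endpoints and the Kaplan-Meier analysis. It names no endpoint, covariates, model or role.
- **Sample size.** The trial is sized on the crude test: "the expected proportion of failure in patients undergoing PSV will be 22" per cent, "we hypothesized a proportion of 15% for patients in the PSV + sigh group", and "Assuming non-inferiority of PSV + sigh treatment, with a tolerance of 5" per cent, giving "a sample size of 258 patients (with 129 patients per study arm") "with power of 0.8 and alpha 0.05".
- **Baseline data (Data collection).** Before the sigh test the sites record, among other things, "severity of lung injury (e.g., ventilation setting, arterial blood gases, respiratory system compliance") and the number of organ failures. The Sigh test section adds the 30-minute change in SpO2/FiO2. The Randomization section places allocation after that test, so all of these values precede randomisation.

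**The concern.** In a randomised trial the reason to adjust is prognosis. Covariates that predict the outcome reduce the variance of the treatment comparison, and confounding at baseline is dealt with by the allocation itself. The plan gives confounding as its reason and leaves the prognostic information out of the primary test.

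The baseline values plausibly matter for this endpoint because some of them measure how far a patient starts from a failure threshold. Patients enter with PEEP from 5 to below 15 cmH2O and PaO2/FiO2 above 100 and up to 300 mmHg (Study population). PEEP of 15 or more counts as failure (Primary endpoint). PEEP of 15 or more, or PaO2/FiO2 of 100 or less, also indicates a switch to controlled ventilation, which counts as failure if it lasts 24 h. The Discussion describes severity of lung injury at presentation as a main determinant of outcome.

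Precision is what is at stake. The trial has about 80% power, and only if sigh lowers failure by 7 points.

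**Working it through.** **Inputs.** From Sample size: control failure 0.22, sigh failure 0.15, margin 0.05, power 0.80, 129 per arm. From Statistical analysis: one-sided alpha 0.05. The proportion of outcome variance explained by baseline values (R²) is not in the documents. It is assumed here and shown as a range.

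**Step 1: reproduce the plan's figure.** For a failure outcome, the distance from the expected difference to the margin is 0.05 + (0.22 − 0.15) = 0.12.

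n = [0.22×0.78 + 0.15×0.85] × (1.645 + 0.842)² / 0.12² = 0.2991 × 6.183 / 0.0144 = 128.4, rounded up to **129 per arm**. This matches the plan.

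**Step 2: power of the crude test at 129 per arm.**

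SE = √(0.2991 / 129) = 0.0482.

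Power = Φ(0.12 / 0.0482 − 1.645) = Φ(0.847) = **80.2%**.

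The one-sided bound extends 1.645 × 4.8 = 7.9 points above the estimate. Sigh must therefore be observed about 2.9 points better (7.9 − 5) to meet the margin, which is about 4 patients in 129.

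**Step 3: power with adjustment.** Multiply the SE by √(1 − R²). The equivalent crude sample size is 129 / (1 − R²).

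| Assumed R² | Power at 129 per arm | Equivalent crude n per arm | Narrowing of the interval |
|---|---|---|---|
| 0 | 80.2% | 129 | 0% |
| 0.05 | 81.9% | 136 | 2.5% |
| 0.10 | 83.7% | 143 | 5.1% |
| 0.15 | 85.5% | 152 | 7.8% |

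**Step 4: check by simulation.** Each scenario used 4,000 trials with 129 per arm and one baseline score. A logistic model was standardised to a risk difference and its one-sided bound compared with 5 points. Power is at 22% vs 15%. Type I error is at the margin (20% vs 25%).

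| AUC of the score | Variance reduction | Crude power | Adjusted power | Adjusted type I error |
|---|---|---|---|---|
| 0.64 | 3.1% | 80.6% | 81.5% | 4.4% |
| 0.69 | 9.8% | 80.3% | 83.5% | 4.8% |
| 0.74 | 11.5% | 81.0% | 85.7% | 4.8% |
| 0.80 | 19.7% | 80.6% | 86.9% | 4.7% |

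The simulation broadly agrees with the formula, and the error rate stays below 5%.

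**Step 5: events available for a model.** 0.22 × 129 + 0.15 × 129 = 28.4 + 19.4 ≈ 48 expected failures.

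**Step 6: what adjustment does not cure.** If failure is 22% in both arms, power is about 25% crude and about 27% with R² = 0.10. Adjustment does not replace the hoped-for 7-point benefit.

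**The case against.** The strongest reply is that nothing here is wrong. The crude test is valid, fixed in advance, consistent with the sample size and directly readable against a 5-point margin. The article is a condensed account, and the full protocol or analysis plan may name covariates and a model. All of that stands, and it limits the point to lost efficiency and one poorly reasoned sentence.

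A reader might go further in four ways that the document does not support:

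- **That the primary analysis is left open to a post hoc choice.** It is not. The test, margin and level are stated, and the adjustment sentence does not refer to the primary test. Any open choice concerns additional adjusted analyses, and the Discussion says that all analyses will be done blinded.
- **That the baseline predictors are strong.** No R², AUC or odds ratio for the failure composite is given. Eligibility narrows the range of PEEP and PaO2/FiO2. Several routes to failure, such as arrhythmia, agitation or reintubation for secretions, are not driven by oxygenation.
- **That the plan would set an odds ratio against a 5-point margin.** The text names no logistic model and no odds ratio. The scale matters only for how a fix is written.
- **That the missing covariate list is itself a defect.** Such lists commonly sit in documents not shown here.

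It is also fair to say that an adjusted primary analysis brings choices on covariate form, missing values and variance method, and that about 48 events will not carry many covariates.

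**Conclusion.** The point holds as a free improvement. It does not show an error in the primary test, which meets its stated power under the plan's own inputs.

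Pre-specified adjustment would add about 1.7 to 5.3 power points (81.9% to 85.5%) if baseline values explain 5% to 15% of outcome variance. It would add one to two points or less if they are weak. This range rests on an assumed R² and on the plan's 22% and 15% failure proportions. That the listed covariates predict failure is a plausible inference from the endpoint's thresholds; the document does not demonstrate it.

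Separately, the confounding rationale is unsuited to a randomised comparison, whatever an unseen analysis plan adds.

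**What to change.** Before any comparison by arm:

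1. Make the primary estimate a covariate-adjusted risk difference. Fit a logistic model with arm and a short fixed list such as baseline PaO2/FiO2, PEEP and number of organ failures, and optionally the sigh-test change in SpO2/FiO2. Standardise it to the trial population. Compare its one-sided 95% upper bound (robust or bootstrap standard error) with the same 5-point margin, so that the margin keeps its meaning.
2. State the form of each covariate and the handling of missing baseline values. Keep the list short in view of the expected events.
3. Keep the crude test as a sensitivity analysis.
4. Replace the confounding sentence with one giving prognosis as the reason for adjustment and the role of any adjusted analysis.

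If the crude test is kept as primary, the minimum is to say so, label adjusted analyses as supportive, and name one adjusted risk difference with its covariates.

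The cost is analysis-plan wording and minor programming. No extra patients or data are needed, and the sample size stays at 129 per arm.

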### Study organization

The steering committee is composed of two principal investigators (TM and LB) plus seven international experts on ventilation who contributed to the design and revision of the study protocol. Each participating center will indicate a local investigator in charge of the study. The principal investigators are responsible for administrative management and communication with the local investigators and for helping the participating clinical sites in trial management, record keeping and data management. The local investigators provide structural and scientific leadership. They guarantee the integrity of data collection and ensure timely completion of the case report forms.

Collected data will be entered in an electronic case report form (eCRF) available online at a dedicated website (https://sighprotection.digitalcrf.eu), with protected individual access for each participating center. Patient data will be anonymous and coded according to a number. The eCRF includes tools to promote data quality, such as range checks for data values. Data monitoring will be performed by means of queries on the database done by statisticians and analyzed to identify abnormalities and inconsistencies.

Based on clinical experience and results of physiologic studies, the additional risks for patients enrolled in the PSV + sigh arm is expected to be minimal in comparison to standard of care. Still, specific patient insurance will be granted to cover all unexpected adverse events caused by the study interventions and all adverse events will be monitored by and reported to the coordinating center.

## Discussion

PROTECTION is a pilot randomized controlled trial to test the long-term clinical feasibility of the addition of sigh to PSV in comparison to standard PSV. If positive, it will provide the basis for a future larger trial aimed at verifying the impact of PSV + sigh on a composite outcome endpoint including 28-day survival and ventilator-free days. Moreover, it will provide physicians a physiologically sound addition (i.e., sigh) to standard PSV for lung protection able to favor assisted ventilation.

Mortality remains considerably high (around 40%) in intubated patients with AHRF [6]. The clinical severity of lung injury at presentation and early appropriate treatment are the main determinants of patients’ outcomes [19]. However, while the lungs recover, VILI might significantly impact survival [1]. Recent studies testing strategies that enhance lung protection (e.g., early referral to an extracorporeal membrane oxygenation (ECMO) center [22]; use of muscle relaxants during the first 48 h after intubation [23]; early use of extended sessions of prone positioning [24]) yielded significantly decreased mortality. However, such trials enrolled only the most severely ill patients with AHRF on controlled mechanical ventilation. A recent large observational study [6], instead, showed that most ventilated patients admitted to the ICU have mild to moderate AHRF or ARDS that leads to considerably high mortality (≈ 35%) anyway. Moreover, the same study reported that around 30% of invasively ventilated patients with AHRF and ARDS are on some form of spontaneous breathing from day 1 after intubation, independent of the severity of their illness [6], and this proportion likely increases within 1 week. Thus, there is an urgent need for interventions that increase lung protection during assisted ventilation.

Key determinants of VILI in patients with AHRF undergoing assisted ventilation include elevated ventilation pressures and inspired fraction of O_2_ (FiO_2_) [25]; heterogeneous distribution of alveolar collapse that increases the regional tidal volume/end expiratory lung volume (Vt/EELV) ratio (i.e., the regional lung strain) [8] and strenuous inspiratory effort and low regional compliance that determines elevated regional transpulmonary pressure (i.e., the regional lung stress) [10]. To this end, previous studies showed that the addition of sigh to assisted mechanical ventilation improves oxygenation without increasing ventilation pressures and FiO_2_; decreases the tidal volumes by decreasing the patient’s inspiratory drive; increases the EELV by regional alveolar recruitment; decreases regional heterogeneity of lung parenchyma; decreases patients’ inspiratory efforts limiting transpulmonary pressure and improves regional compliance [11–16, 26]. Of note, the improvement in gas exchange and lung mechanics disappears after sigh discontinuation [12]. In conceiving this study, we reasoned that long-term application of sigh during PSV might decrease the risk of VILI through various synergic mechanisms, possibly decreasing the duration of mechanical ventilation and mortality in patients with AHRF. To date, no RCT has tested the long-term safety and feasibility of the application of sigh. Therefore, before testing the effects of sigh on clinical outcome in a RCT, the feasibility of long-term use of sigh had to be investigated: this is the primary aim of the PROTECTION trial. Moreover, data on the safety of sigh will be collected, evaluating potential adverse effects including development of pneumothorax or other signs of barotrauma and hemodynamic instability. Finally, the sample size was calculated based on a potential deacrese in failure to remain on assisted ventilation from 22% during PSV to 15% during PSV + sigh, so that the potential to promote spontaneous breathing by addition of sigh will already be tested.

We anticipate the PROTECTION trial to be highly feasible, as study procedures are mainly limited to ventilation settings and do not include complex interventions, with limited burden on daily activities. PSV + sigh is an easy-to-implement ventilation mode and, for the present study, we will use high-performance ICU ventilators already available in each clinical unit, dramatically decreasing the study costs.

Even though PROTECTION might be a largely pragmatic study, the protocol specifically suggests adjustments of ventilation settings and weaning procedures. Moreover, criteria for switch to controlled ventilation, use of rescue therapies and reintubation are pre-defined by the study protocol. Since return to controlled mechanical ventilation can occur due to reasons not related to failure of assisted ventilation (e.g., necessity to perform diagnostic or therapeutic procedures requiring deep sedation and neuromuscular blockade), the protocol stresses the importance of periodic reassessment (at least every 8 h) to restore assisted ventilation as soon as clinical conditions permit. To this end, failure of assisted ventilation is defined when controlled ventilation is maintained for at least 24 h. In summary, the PROTECTION study protocol limits discretional settings and clinical decisions that might interfere with the primary outcome.

One important limitation of the PROTECTION trial is that blinding is not possible due to the nature of the intervention, and this could induce bias. However, all the processes that can influence the primary outcome are regulated by the protocol and all the analyses will be performed in a blinded fashion. Second, even though a lower sigh rate might be regarded as more physiological [15], in the absence of conclusive data on sigh “minimum effective dose” [14], we chose a rate of one per minute because this can be performed by all the clinically available high-performance ICU ventilators, increasing feasibility and decreasing costs, especially of the future larger RCT. Finally, we did not plan any biomolecular analysis to verify the impact of addition of sigh on lung protection for budget reasons; in any case, we will collect a huge amount of physiological data during the whole study period that will allow reconstruction on mechanistic effects underlying the clinical benefits.

In conclusion, PROTECTION is a pilot randomized controlled trial to test the feasibility of long-term addition of sigh to PSV. Its results could provide a ready-to-use treatment enhancing successful application of assisted ventilation. Moreover, PROTECTION will be the basis for planning a future larger trial investigating the use of sigh as a strategy to improve hard clinical outcomes in patients with AHRF undergoing assisted ventilation through enhanced lung protection.

## Trial status

The PROTECTION trial is currently recruiting patients. The protocol was approved by the coordinating center Institutional Review Board on 12 June 2017. The first patient was enrolled on 20 December 2017. Sixteen centers already received approval from the local ethical committees and are actively recruiting patients. Recruitment is expected to be completed in November 2019.

## Abbreviations

AHRF: Acute hypoxemic respiratory failure
ARDS: Acute respiratory distress syndrome
CONSORT: Consolidated Standards of Reporting Trials
ECMO: Extra-corporeal membrane oxygenation
eCRF: Electronic case report form
EELV: End-expiratory lung volume
ESICM: European Society of Intensive Care Medicine
FiO_2_: Fraction of inspired oxygen
ICU: Intensive care unit
PaCO_2_: Partial arterial pressure of carbon dioxide
PaO_2_: Partial arterial pressure of oxygen
PBW: Predicted body weight
PEEP: Positive end-expiratory pressure
PSV: Pressure support ventilation
RASS: Richmond Agitation-Sedation Scale
RCT: Randomized controlled trial
RR: Respiratory rate
SBP: Systolic blood pressure
SBT: Spontaneous breathing trial
SOFA: Sequential Organ Failure Assessment
SPIRIT: Standard protocol items: recommendation for interventional trials
SpO_2_: Pulse arterial oxygen saturation
VILI: Ventilator-induced lung injury
Vt: Tidal volume
